### Content of the Interventions

The *Daybreak* program is designed for people looking to change their relationship with alcohol. It allows participants to set a goal, reflect on their mood, and engage with peer support. *Daybreak* helps people to change their relationship with alcohol in 4 ways.

The first one is weekly check-ins. *Daybreak* supports members in a self-reflection process to discover their inner drivers. With the help of Australia’s leading experts in motivational interviewing, *Daybreak* has created a set of self-report questionnaires (Multimedia Appendix 2) that are designed to help people uncover their intrinsic motivators for change.

The second one is peer support. *Daybreak* connects members to the *Daybreak* Community, a channel to immediate empathy, problem solving, and accountability. Currently, 45% of shares in *Daybreak* receive 5 or more comments within an hour. The program supports a vibrant community with members who care for each other, help each other navigate tough times, and keep each other in check.

The third one is behavioral experiments. *Daybreak* encourages members to take experiments and reflect on their learnings. Designed by the Hello Sunday Morning Clinical Team, these experiments draw on techniques from cognitive behavioral therapy, motivational interviewing, and acceptance and commitment therapy. There are a range of experiments across 5 areas including mindfulness, connectedness, resilience, situational strategies, and health. Mindfulness experiments help members learn how to be in-the-moment and recognize when a drinking trigger has been activated. The connectedness experiments help them to connect with others in a meaningful and healthy way without alcohol. The resilience experiments teach them how to bounce back from negative experiences and lapses. The situational experiments provide strategies for a range of common trigger situations. Finally, the health experiments assist members in establishing good fitness routines, good eating and sleeping habits, and general health strategies to help with regulating mood (Figure 2).

The fourth one is health coaches. All health coaches meet the low-intensity mental health guidelines set by the Australian Government Department of Health [58]. Specifically, this includes a minimum certificate IV in a mental health or community services discipline. The clinical team of health coaches at Hello Sunday Morning all meet this minimum criterion, as well as having specific alcohol and other drug training and experience. Some coaches are registered General and Clinical Psychologists.

Health coaches are required to undertake in-house training, which includes modules on health coaching and how it differs from therapy, ethical considerations when providing Web-based services, alcohol facts and management strategies, forming connections during online support, motivational interviewing, case studies and ethical dilemmas, coaching procedures, risk management, as well as platform-specific training modules. They undergo a period of supervision on initial interactions with participants and then periodically receive feedback from a senior health coach. Health coaches also participate in fortnightly peer supervision for case discussion and receive individual supervision with an Australian Health Practitioner Regulation Agency–approved supervisor who is a clinical psychologist, when needed.

Health coaches partner with members to help them set and reach goals for satisfying and healthy lives. The coaching service is conducted via real-time chat-based messaging on a secure platform. Health coaches again use cognitive behavioral therapy, motivational interviewing, and acceptance and commitment therapy techniques. Coaches tailor support and the approaches used to suit the member’s needs.

### Analysis

We will evaluate the primary and secondary outcome using an intention-to-treat approach with the effect of the intervention on each measure being assessed via a time-by-group interaction. Due to the correlated data arising from the repeated measures, we will employ a multilevel mixed effects regression model with a random intercept term. This will control for clustering of variance within individuals over the repeated measures. For continuous data, we will use an unstructured correlation matrix with a normal distribution and identity link. For other types of data (eg, count, categorical), multinomial, Poisson, or negative binomial distribution will be used with their appropriate link functions. A sensitivity analysis will include use of specialist alcohol services or alcohol pharmacotherapy as a covariate.

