Australian users of Hello Sunday Morning are more likely to be female (61%) than male, with most aged less than 50 years (89%). Few (5%) are classified as low-risk alcohol users as assessed by the alcohol use disorders identification test [40] (AUDIT) (score=0-7), with 42% classified in the hazardous or harmful range (AUDIT 8-19) and 53% classified as probably dependent (AUDIT≥20) [35]. Limited follow-up data (n=49) on a subsample of Victorian Hello Sunday Morning participants (n=345) found that the prevalence of probably dependent drinkers fell from 45% at baseline to 7% at 1 month and 24% at 3 months [41].

The aim of the study was to evaluate the effectiveness of the online coaching component of the *Daybreak* program in reducing alcohol consumption via a randomized controlled trial. The *Daybreak* program is a smartphone app developed by Hello Sunday Morning, based on the original Web-based program. *Daybreak* consists of the same social-networking peer-support forum as the Hello Sunday Morning program but also includes clinically based activities known as behavioral experiments and chat-based coaching. The primary hypothesis is that those randomized to receive *Daybreak* including peer-support, behavioral experiments (see *Content of the interventions* for details) plus online coaching, will show a greater reduction in alcohol-related problems that those randomized to just access the *Daybreak* program including peer-support and behavioral experiments (without online coaching). Consistent with the literature, the secondary hypotheses are that greater improvements will be shown for those with lower AUDIT scores (8-19), than those in the higher score category (≥20), and finally, greater improvements are expected for male participants [15,42].

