### Participants and Randomization

All new registrants to *Daybreak* will receive information about the study: it is anticipated that no additional advertising will be required. To be eligible for the study, participants must be aged 18 years or older, score 8 or more on the [44] AUDIT, and be resident in Australia. Participants also require a valid email address and access to the internet. We will exclude those who have ever received treatment for cardiovascular disease, due to the risks for this latter group [45]. In addition, the screening questions include the P4 suicidality screening survey [46]. Those scoring above minimal risk will still be eligible for the study but will receive details of a national, 24-hour crises support line (lifeline).

Regardless of the group to which they are randomized, those scoring 20 or more on the AUDIT (probable dependence) will be eligible for inclusion in the study but will also be advised to seek in-person guidance from their general practitioner or other clinician before reducing their alcohol consumption, to minimize the risk of serious complications from alcohol withdrawal. Given the large sample, simple fully automated randomization will be implemented. Participants will be blind to their group allocation—all will receive an active treatment. Participants access the platform by logging in with their email address and password.

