**Figure 1 figure1:**
[figure not shown]
Flowchart of participants through the trial.

The effect sizes for Web-based SBI alcohol interventions are in the range *d*=0.3-0.4 at 6 months [19-21]. On the basis of a small estimated effect size of *f=* 0.10 (equivalent an effect size of *d*=0.2) at 6 months, with a correlation between repeated measures of *r*=0.5, we will require 60 people per group for the main analysis based on power of 0.80 and alpha set to *P*<.05. Given the interest in the effectiveness of interventions by gender and for those with probable dependence (assessed via the AUDIT), the objective will be to recruit approximately 60 people in the smallest cell(s). From demographic data [35] with about 50% of the *Daybreak* population likely to be in the probable dependence AUDIT category and 40% being male, to obtain about 60 people in this cell will require 300 people per study arm (600 in total). To allow for attrition, the target will be to recruit 467 per arm (N=934), with 35% lost to follow-up.

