### Outcome Measures

All measures will be assessed at each time point except the AUDIT (baseline only) and adverse events [47] (baseline and the final time point; see Table 1). The primary outcome will be change in AUDIT-consumption (AUDIT-C) scores. The AUDIT was developed by the World Health Organization and validated in a range of countries, including Australia [44]. It has a range of 0-40: a threshold of 8 or more will be used as a screening measure to identify eligible participants at baseline. With follow-up at 1, 3, and 6 months, the change in the first 3 questions (known as the AUDIT-C) will be the primary outcome and used to assess change in alcohol use (as some of the other AUDIT questions use a reference period of the last 12 months). The AUDIT-C has also been shown to predict clinical outcomes at 1 year [48]. The secondary outcomes will be changes in:

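### The primary AUDIT-C model, as stated, leaves out gender and baseline AUDIT severity; pre-specifying both with visit interactions is a small, nearly free improvement

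*Protocol article*

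**What the plan says.** All references are to the protocol article.

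- **Outcome Measures:** "The primary outcome will be change in AUDIT-consumption (AUDIT-C) scores". Table 1 schedules AUDIT-C at baseline, 1, 3 and 6 months, and the full AUDIT and demographics at baseline only.
- **Analysis:** the plan has "the effect of the intervention on each measure being assessed via a time-by-group interaction", and "we will employ a multilevel mixed effects regression model with a random intercept term". It adds: "For continuous data, we will use an unstructured correlation matrix with a normal distribution and identity link". The only covariate named comes last: "A sensitivity analysis will include use of specialist alcohol services or alcohol pharmacotherapy as a covariate".
- **Introduction, secondary hypotheses:** better results are predicted for AUDIT 8-19 than for AUDIT 20 or more, and "greater improvements are expected for male participants".
- **Sample Size:** "Given the interest in the effectiveness of interventions by gender and for those with probable dependence", the trial is sized on the smallest gender-by-dependence cell, with 35% loss expected.
- **Participants and Randomization:** "Given the large sample, simple fully automated randomization will be implemented".

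**The concern.** Gender and AUDIT severity drive the secondary hypotheses and the sample size, yet the Analysis section does not place them in the primary model. The one covariate it names is service or medication use. Health resource use is recorded at every visit, so this covariate does not stand in for a baseline factor.

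Two things are at stake. The first is precision: baseline variables that predict change reduce the residual variance of the coaching contrast. The second is dropout. A likelihood-based mixed model is valid under missing-at-random given what the model contains. Baseline AUDIT-C carries part of severity but not all of it, because it has three consumption items while the 20-or-more category uses the full 0-40 score. Gender is not carried at all. Only one arm has a human coach, so the type of participant who stays could differ by arm.

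**Working it through.** **1. The plan's own figure.** Taking its 60 per cell as given: 60 / (0.5 × 0.4) = 300 per arm, and 300 / (1 − 0.35) = 461.5, so 462. The plan states 467. The gap is immaterial: 467 × 0.65 = 303.6, so about 304 completers per arm.

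**2. Inputs.** From Sample Size: d = 0.2, r = 0.5, 50% with probable dependence, 40% male, 35% loss. Assumed, because the document gives no value: each factor shifts change by 0.2 to 0.5 SD.

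**3. Precision in closed form.** The SD of change is √(2(1 − 0.5)) = 1. Two binary factors with effect c explain c²(0.5 × 0.5 + 0.4 × 0.6) = 0.49c² of its variance.

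- c = 0.2: 0.0196, so the standard error ratio is √(1 − 0.0196) = 0.990.
- c = 0.5: 0.1225, so the ratio is 0.937.

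For the 6-month change contrast at 304 per arm, the unadjusted SE is √(2/304) = 0.0811 and power is Φ(0.2/0.0811 − 1.96) = 0.694. With the factors it is 0.702 (c = 0.2) or 0.749 (c = 0.5). That is worth 467 × 0.0196 ≈ 9 to 467 × 0.1225 ≈ 57 participants per arm. These powers are for one contrast and do not test the plan's repeated-measures power statement; only the differences matter here.

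**4. Precision by simulation.** Settings: 467 per arm, four visits, unstructured covariance, 250 runs per scenario. Entries are the mean SE of the 6-month group-by-time contrast.

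| Data | c | No covariates | Main effects only | With visit interactions |
|---|---|---|---|---|
| Complete | 0.2 | 0.0661 | 0.0661 | 0.0655 |
| Complete | 0.5 | 0.0692 | 0.0692 | 0.0653 |
| 35% loss | 0.2 | 0.0773 | 0.0769 | 0.0762 |
| 35% loss | 0.5 | 0.0811 | 0.0802 | 0.0762 |

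Under 35% loss, visit interactions cut the SE by 1.4% to 6%. Main effects cut it by only 0.5% to 1.1%, and by nothing with complete data. A term that is constant over visits cancels from a within-person contrast.

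**5. Dropout, moderate case (assumed).** Retention for AUDIT 8-19 / 20 or more is 75/55% or 80/50% with coaching and 65/65% without. AUDIT 20 or more predicts a score 0.3 to 0.4 SD worse. The severe share among completers is then 0.55/1.30 = 0.423 or 0.50/1.30 = 0.385 with coaching, against 0.500 without. With no credit for any AUDIT-C data, the bias is at most (0.500 − 0.423) × 0.3 = 0.023 to (0.500 − 0.385) × 0.4 = 0.046 SD.

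Baseline and interim AUDIT-C carry some of the severity information and reduce this. Simulated bias is 0.020-0.033 SD if all loss precedes month 1, and 0.008-0.025 SD once interim visits contribute. Rounded, that is 0.01 to 0.03 SD, or 5% to 15% of d = 0.2. At SE 0.0773 the false-positive rate Φ(b/SE − 1.96) + Φ(−b/SE − 1.96) is 5.2% at b = 0.01 and 6.7% at b = 0.03. If severe drinkers leave the coached arm, the bias favours coaching.

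**6. Dropout, other cases (same simulation as step 4; Monte Carlo error about 0.005 SD).**

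| Dropout pattern | c | No covariates | Main effects only | With visit interactions |
|---|---|---|---|---|
| Same in both arms | 0.2 | −0.001 | −0.001 | 0.000 |
| Same in both arms | 0.5 | +0.003 | +0.002 | +0.001 |
| Opposite by arm, deliberately strong | 0.2 | −0.064 | −0.029 | +0.005 |
| Opposite by arm, deliberately strong | 0.5 | −0.120 | −0.080 | +0.002 |

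The strong case assumes opposite log-odds of dropout in the two arms, 1.0 for severity and 0.6 for gender.

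**The case against.** **The article is silent; it does not exclude.** It never says that no other covariates will be used, and a full analysis plan may list them. This stands. A reader might infer that the protocol has fixed a wrong model, and the text does not support that. What can be said is that the model, followed as written, omits two factors the document itself treats as important.

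**Nothing says that dropout differs by arm.** Sample Size gives only an overall 35%. Both arms have the same survey schedule and reminders, and the research assistant who calls is blind to allocation. This also stands: with the same pattern in both arms the bias is about nil. A reader might infer that 35% loss biases the planned result; the documents do not show that. Adjustment also helps only as far as these factors explain who leaves.

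**The hypotheses may be about effect modification.** The predictions for men and for AUDIT 8-19 can be read as larger coaching effects rather than larger change in general. Covariate-by-visit terms do not test that; the subgroup analyses need terms that also involve group. The prognostic reading is plausible but not certain.

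**The full AUDIT contains the AUDIT-C items.** If baseline AUDIT-C is kept as a response, the severity covariate overlaps with it. Its baseline coefficient then has no clean meaning, but severity is measured before randomisation, so the group contrast is not distorted.

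**Allocation.** A reader might conclude that simple randomisation should be replaced by stratification. The figures do not support this. With 304 completers per arm, the SD of the between-arm difference in severe share is √(2 × 0.25/304) = 0.041. At effects of 0.2 to 0.5 SD that is a chance shift of 0.008 to 0.020 SD. The mean efficiency loss is under 1%, and enrolment has begun.

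**Conclusion.** The point holds as a modest improvement, not as an error in the plan. Under assumed effects of 0.2 to 0.5 SD on change, both factors with visit interactions reduce the standard error of the coaching contrast by about 1% to 6%. The more useful gain is a more credible missing-at-random assumption. Avoidable bias is about 0.01 to 0.03 SD if severity-related dropout differs moderately by arm, 0.06 to 0.12 SD in a deliberately extreme case, and about nil if the pattern is shared.

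A larger power claim is tempting. Treating baseline AUDIT-C as a covariate and adding further baseline predictors gives power of 81% rising to 83% under assumed correlations, but that is not the change contrast the protocol states, so it should not be used.

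**What to change.** In the Analysis section, add one sentence: the primary AUDIT-C model includes gender and baseline AUDIT severity (8-19 versus 20 or more, or the full score) as fixed covariates, each with a visit interaction. The baseline 7-day diary total may be added in the same way but is optional. The subgroup hypotheses still need their own interaction terms with group.

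The cost is a slightly longer model, with no additional data or participants. The Results section says that analysis has not begun, so the choice can still be pre-specified; made after results are seen, it would be less credible. Leave the randomisation scheme unchanged.

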### Participant Safety

There are a number of mechanisms in place for forum monitoring (eg, blog posts and comments). The first is an automated system that alerts the clinical team when a member writes a post including a trigger word and receives more than 30 comments. Trigger words are predetermined words that may indicate a member is at risk (eg, kill, suicide, hurt, end it, no meaning, hopeless, cannot cope, die). Second, the forum is monitored by support staff and the clinical team, who will intervene on a thread if needed and contact the member privately via email. Third, members are able to report posts to *Daybreak* administration if they are concerned about a member or their post.

The existing *Daybreak* Risk Management Protocol will be used for all participants in the *Daybreak* research trial who report serious mental health concerns, suicidality, self-harm, family violence, or risk to children. Although there are procedures in place for each concern, they typically include working collaboratively with the member to keep them safe, deescalating the situation and implementing a safety plan, as well as encouraging them to contact suitable referrals (eg, specific or face-to-face services) provided by health coaches.

**Table 1 table1:** Data collection schedule.

Measure	Baseline	1 month	3 months	6 months
Demographics	✓			
Drinking diary	✓	✓	✓	✓
AUDIT^a^	✓			
AUDIT-C^b^	✓	✓	✓	✓
K-10^c^	✓	✓	✓	✓
Days out of role	✓	✓	✓	✓
Health resources	✓	✓	✓	✓
Sleep quality	✓	✓	✓	✓
Exercise	✓	✓	✓	✓
Quality of life	✓	✓	✓	✓
Adverse events	✓			✓

^a^AUDIT: alcohol use disorders identification test.

^b^AUDIT-C: alcohol use disorders identification test-consumption (items 1-3).

^c^K-10: Kessler 10.

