**Figure 2 figure2:**
[figure not shown]
Example of Daybreak behavioral experiments.

The Hello Sunday Morning site and intervention are not designed to provide support for emergency situations, such as severe withdrawal symptoms (seizure or delirium tremens) or severe psychological distress. In a general hospital sample, 0.65% incurred either a seizure or delirium tremens [59], but in an alcohol detoxification inpatient sample, 5.6% had delirium tremens and 7.4% had seizures [60]. Therefore, anyone scoring 20 or more on the AUDIT will be advised to seek medical guidance before reducing their alcohol use. We will also recommend that anyone who has ever incurred a seizure or delirium tremens seek advice. In addition, we will provide details of national hotlines for psychological problems.

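### As written, the automated forum alert needs both a trigger word and more than 30 comments, so a little-answered post with a suicide or self-harm word raises no automated alert

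*Protocol article*

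**What the plan says.** The Participant Safety section of the protocol article lists three ways in which the forum is watched.

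- Listed first is an automatic alert, described as "an automated system that alerts the clinical team when a member writes a post including a trigger word and receives more than 30 comments". The sentence that follows gives the purpose and some examples: "Trigger words are predetermined words that may indicate a member is at risk (eg, kill, suicide, hurt, end it", with further examples after these.
- The second is human monitoring: "the forum is monitored by support staff and the clinical team, who will intervene on a thread if needed", with private email contact to the member.
- The third is that members can report posts that worry them.

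The same section refers to an existing Risk Management Protocol for participants who report suicidality, self-harm and similar concerns. After Figure 2 it adds that "we will provide details of national hotlines for psychological problems".

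Two other sections bear on the point. Participants and Randomization describes a suicidality screen at entry: "Those scoring above minimal risk will still be eligible for the study but will receive details of a national, 24-hour crises support line". Content of the Interventions gives the only figure on forum activity, namely that 45% of shares "receive 5 or more comments within an hour".

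**The concern.** The trigger-word list exists to pick out posts whose author may be in danger. That signal is complete when the post is written. The second condition counts how many replies other people have made, and the article nowhere says that reply volume indicates risk. Requiring both conditions silences the alert for the post that few people answer and delays it for every other post.

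What is at stake is participant safety. Both arms use the forum, people above minimal risk on the suicidality screen can be enrolled, and this is the only automated forum safeguard the article names. If it works as described, detecting an at-risk post with few replies depends on a staff member or another participant happening to notice it. The point does not touch the sample size, the outcomes or the analysis.

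**Working it through.** The article has no figure of its own to reproduce here, and the main check is a reading of the rule.

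**The rule.** One *when* governs two conditions joined by *and*:

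alert = (post contains a trigger word) AND (comments > 30).

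*More than 30* means at least 31. The cases are:

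| Trigger word in post | Comments | Automated alert as written |
|---|---|---|
| Yes | 31 or more | Yes |
| Yes | 0 to 30 | No |
| No | 31 or more | No |
| No | 0 to 30 | No |

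The second row is the defect. A post that ends up in the first row raises its alert only when the 31st comment arrives.

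**Is it corrected elsewhere?** No other section of the article describes an automated alert on a trigger word alone. The remaining safeguards compare with the automated alert as follows:

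| Safeguard | Depends on comment count? | Replaces automated detection of a post? |
|---|---|---|
| Monitoring by staff and clinicians | No | No: a person must see the post, and no frequency or response time is given |
| Reports by members | No | No: a person must see the post and act |
| Crisis line offered after the entry screen | No | No: it informs the participant and alerts nobody |
| National hotline details | No | No: same reason |
| Risk Management Protocol | Not stated | Not as described: it covers participants who report a concern, and the article does not say that it detects posts |

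**Context for the threshold of 30.** The only input is the 45% of shares with 5 or more comments within an hour (Content of the Interventions).

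- Shares with 4 or fewer comments at one hour: 100% − 45% = 55%.
- Further comments such a share needs to reach the threshold: at least 31 − 4 = 27.
- Shares that could meet the comment condition within the first hour: at least 0% and at most 45%, since any share with 31 comments is among those with 5 or more.

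These figures describe all shares in their first hour. They do not describe trigger-word posts or eventual comment counts, so they show only that 31 is a high bar early on. The reading of the rule does not depend on them.

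**The case against.** The strongest reply is that this is a slip of the pen. The sentence is loosely built: grammatically it is the member who receives the comments, not the post. Two separate alerts, one for a trigger word and one for a very busy thread, may have been compressed into one clause. The operating rule may also sit in the Risk Management Protocol, which is not shown. This stands as a caution: the text establishes what the article says, not how the software behaves. It does not remove the point, because the published safety description then needs correcting.

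A second reply is that the article presents three parallel mechanisms and does not call the automated alert the main one. Human monitoring and member reports do not depend on the comment count. That is true and lowers the likely harm. Both still rely on someone noticing the post, which is the gap an automated alert is meant to close.

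A third is that some listed words, such as *hurt* or *die*, are common, so a filter against false alarms may be deliberate. The article gives no such reason. Under the literal rule the alert is narrowed and delayed rather than void, and that is a fair limit on how strongly the point should be put. Even so, reply count is a poor filter, because it tracks other members' attention and not the author's risk.

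Finally, the first-hour figures say little about trigger-word posts. That is accepted, and they carry no weight in the conclusion.

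**Conclusion.** The concern holds as a statement about the text. As written, a post with a suicide or self-harm word and 30 or fewer comments raises no automated alert, and no other section supplies a trigger-word-only alert. The rule works against the purpose that the next sentence of the article gives for the trigger words.

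The share of at-risk posts affected cannot be stated from the article. The finding assumes that *and* means both conditions are required, which is the ordinary reading. Whether the live software behaves this way is unknown and can be settled by checking the setting. The point should be fixed because it concerns participant safety and the remedy is small. It is tempered by the other safeguards and has no bearing on the sample size or the analysis.

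**What to change.** Make a trigger word sufficient on its own to alert the clinical team, as soon as the post is made. If a comment-count alert is wanted, keep more than 30 comments as a separate, additional trigger. The Participant Safety section could read: *The clinical team is alerted automatically when a post contains a trigger word, whatever its number of comments; a thread with more than 30 comments raises a separate alert.*

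The sponsor should first check the live setting. If the software already alerts on the word alone, only the sentence needs correcting. If it works as described, one rule in the existing system needs changing.

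The cost is a wording correction or a single software change, and afterwards more alerts for the clinical team to review, some of them false.
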